#### Sensitivity analyses

We have pre-specified a number of sensitivity analyses to assess the robustness of our findings:

#### Alternative outcome definitions

1. Hospitalization for lower respiratory tract infection in the first two years of age:
  - a) We will model the total number of hospitalizations per child in the first two years after birth rather than the occurrence of any hospitalization. We have opted to use 'any hospitalization' as our primary outcome as it is possible that some subsequent hospitalizations are re-admissions for the same infection rather than new infections.
  - b) We will examine the outcome of RSV bronchiolitis rather than the broader outcome of lower respiratory tract infection (ICD-9 code 466.11; ICD-10 code J21.0).
  - c) We will only include lower respiratory tract infections during the typical RSV season (November to April)
2. Asthma:
  - a) We will examine hospitalization for asthma alone as an outcome (as opposed to a diagnosis using either hospitalization or physician visits)
  - b) We will identify asthma hospitalization in any position of the hospital discharge summary (rather than only in the primary position)
3. Cerebral palsy:
  - a) We will restrict cases of cerebral palsy to those that also have a code for complications including: feeding difficulty/dysphagia; dystonia; spasticity; or developmental delay
  - b) We will restrict analyses to births admitted to hospital prior to May 2011, when a Society of Obstetricians and Gynaecologists of Canada guideline was issued recommending the administration of Magnesium Sulphate for fetal neuroprotection for imminent preterm birth. The guideline recommended administration up to 31+6 weeks, but provided institutional discretion to adopt higher gestational age thresholds (<34 weeks).
4. ADHD:
  - a) We will use define ADHD using physician billing records in addition to N06B prescriptions (ICD-9 code 314.0).

#### Excluding women who may have received corticosteroids in a prior admission

To account for potential under-reporting of antenatal corticosteroids caused by administration during an antenatal hospital admission that did not result in delivery (which is not documented in the BC Perinatal Database), we will conduct an analysis restricted to women with no prior hospitalizations during the pregnancy. We will derive our primary estimates of the effects of corticosteroids (i.e., "per protocol" analysis) in this subgroup.

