## Introduction

Randomized trials have consistently shown that administering antenatal corticosteroids to pregnant women at risk of preterm labour reduces neonatal mortality and respiratory morbidity. As a result, Canadian and international practice guidelines unequivocally advise that all eligible women at 26 to 34 weeks' gestation at risk of an imminent preterm delivery (due to spontaneous onset of labour, preterm premature rupture of membranes, or pregnancy complication indicating an early delivery) should be given antenatal steroids. Antenatal steroids are a *WHO Priority Life-Saving Medicine*, and administration rates are audited as an indicator of perinatal care quality in multiple jurisdictions including Canada.

However, we still lack high quality evidence on the longer-term safety of antenatal corticosteroids. Select studies have signalled that antenatal steroids may have harmful consequences for child neurodevelopment, and obstetrical leaders are beginning to advocate for more restricted use until long-term safety has been convincingly demonstrated. However, generating rigorous evidence on the effects of antenatal steroids for child neurodevelopment is challenging. Follow-up studies of randomized trials were hampered by low follow-up rates and small sample sizes, and observational studies are highly susceptible to confounding. Without high-quality safety evidence, the unproven potential for harm may be causing a treatment with proven neonatal benefits to be withheld unnecessarily.

When randomization is infeasible, regression discontinuity (RD) studies can provide credible causal effect estimates. The design exploits differences in care between individuals immediately on either side of a clinical cut-point as a quasi-randomization tool. With antenatal corticosteroids guidelines recommend administration of corticosteroids up to 33+ 6 weeks' gestation – but not one day later, at 34 weeks+ 0 days, so infants born as little as hours apart have substantially different chances of receiving the treatment. We propose to use this novel design to generate rigorous evidence on the longer-term safety of antenatal steroids. We also propose to examine if antenatal corticosteroid administration's protective effect on respiratory morbidity extends into early childhood.

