## **Data**

Our study cohort will be created through a linkage of British Columbia's comprehensive population-based databases of detailed obstetrical medical records, medication prescriptions, physician billing, hospital discharge records, vital statistics, and kindergarten child development assessments. The linkage will be performed by PopData BC, a multi-university organization that facilitates the use of the province's databases for research purposes. Maternal and infant personal health numbers and dates of birth will be used as unique identifiers. The linked data are accessed in an anonymized format on a secure server to ensure data confidentiality and security. Follow-up data up to March 31, 2018 will be included, ensuring a minimum of 5 years follow-up for all children.

**BC Perinatal Data Registry:** The BC Perinatal Data Registry contains abstracted obstetrical and neonatal medical records for >99% of deliveries in the province since April 1, 2000. Data quality are maintained through the use of provincially-standardized medical record forms, standardized training of abstractors (certified following a 2-year training program), and regular data checks for plausibility and missing values. Validation studies have established the accuracy and completeness of the database.

**Early childhood development data:** British Columbia has been conducting standardized assessments of child development at kindergarten age since 2001 using the Early Development Instrument, a questionnaire used across Canada and internationally. Data are collected in 3-year waves, so are only available for approximately one-third of children in the province a given year.

**Hospital Discharge Abstract Database:** The BC Hospital Discharge Abstract database contains International Classification of Disease (ICD) codes summarizing the diagnoses and procedures for all discharges, transfers and deaths of inpatients in acute care hospitals in British Columbia. We will only use the first 16 diagnostic coding spots, to ensure that the number of diagnostic coding spots is consistent throughout the study period (a greater number of spots are available in more recent years).

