## **Exposure measurements**

**Gestational age** in days will be calculated using the gestational age algorithm used clinically during the study period. The estimate of gestational age will be based on the last menstrual period if this estimate is similar to the estimate based on early ultrasound ( $\leq 5$  days if the ultrasound was performed  $< 14$  weeks;  $\leq 10$  days if the ultrasound was performed  $< 20$  weeks). If the gestational age estimate based on last menstrual period disagrees with early ultrasound, or no last menstrual period estimate is available, the ultrasound estimate will be used. Day-specific estimates of ultrasound-based gestational age are available in the BC Perinatal Data Registry as of April 1, 2008. Prior to this period, we will calculate day-specific gestational age based on the date of the last menstrual period among women

whose ultrasound-based estimate of gestational age (in weeks) is the same or within 1 week of their estimate based on last menstrual period (in weeks). We will use gestational age in days at the time of maternal admission for the delivery as our unit of analysis, which better approximates timing of antenatal corticosteroid administration compared with gestational age at delivery. We will conduct sensitivity analyses to explore the potential for bias due to exclusion of women with missing day-specific gestational age estimates.

Antenatal corticosteroid administration is available in the BC Perinatal Data Registry as a binary variable indicating the administration of corticosteroids during the delivery admission for the purpose of fetal lung maturation. This can be any type of corticosteroid (e.g., betamethasone or dexamethasone) and does not reflect dosing information. This variable is known to underestimate the true administration rates, as administration during an antenatal admission shortly prior to delivery is not captured (i.e., a patient is admitted, receives antenatal corticosteroids, but is discharged without delivering). We will obtain this variable to confirm the change in the probability of receiving antenatal corticosteroids according to gestational age, but are using the gestational age discontinuity, not the provision of steroids *per se*, as our primary exposure.

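### The subgroup that supplies the main per-protocol estimate excludes any hospitalization at any time in pregnancy, which is wider than its stated aim and costs some precision; transfers into the delivery hospital need a rule and a continuity check at 34+0

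*Protocol*

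**What the plan says.** The rule is in the Protocol, *Sensitivity analyses*, under *Excluding women who may have received corticosteroids in a prior admission*: "we will conduct an analysis restricted to women with no prior hospitalizations during the pregnancy". Its reason is under-reporting "caused by administration during an antenatal hospital admission that did not result in delivery". The same paragraph gives the subgroup a leading role: "We will derive our primary estimates of the effects of corticosteroids", which it then identifies as the per-protocol analysis.

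*Exposure measurements* describes the gap more closely. The registry variable covers the delivery admission only, so "administration during an antenatal admission shortly prior to delivery is not captured"; the example given is that "a patient is admitted, receives antenatal corticosteroids, but is discharged without delivering".

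Three other places bear on the point:

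- *Introduction*: guidelines advise steroids for "all eligible women at 26 to 34 weeks" of gestation at risk of imminent preterm delivery.
- *Data*: the hospital discharge file holds codes "summarizing the diagnoses and procedures for all discharges, transfers and deaths of inpatients in acute care hospitals in British Columbia".
- *Statistical analysis*: the coefficient for being below 34+0 is the intention-to-treat effect and the primary estimate. The per-protocol effect divides the outcome jump by the jump in steroid administration, and is to be interpreted cautiously.

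**The concern.** The exclusion has no limit by gestational age, by reason for admission or by interval before delivery. A woman admitted at 10 weeks is dropped just like a woman treated at 32 weeks and sent home. Only the second fits the problem the protocol describes. Dropping the first makes the estimate less precise and does nothing for the accuracy of the steroid variable.

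A separate question concerns women transferred between hospitals. The discharge file covers transfers, and the rule does not say whether a stay at a sending hospital counts as a prior hospitalization. Transfer is decided after gestational age at presentation is known, so it could respond to the 34-week threshold. If transfers are excluded and their frequency steps at 34+0, the subgroup would be selected differently on the two sides. The per-protocol ratio would then enlarge any resulting artefact, because it divides by a steroid jump smaller than one.

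The planned checks would not show this. The list under *Assessing comparability of groups* contains neither prior admission nor transfer, and the protocol does not say that the checks are repeated within the subgroup.

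**Working it through.** **No figure to reproduce.** The protocol gives no share of women with a prior admission, no transfer rate and no subgroup size. The documents supply the cohort of about 16,000 births (*Overview of research plan*), guideline use from 26 weeks (*Introduction*) and the 5-point total EDI difference taken as clinically significant (*Child health outcomes*). Every other input below is assumed.

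**Step 1: purpose against rule.**

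| | Stated problem | Rule as written |
|---|---|---|
| When | shortly before delivery | any time in the pregnancy |
| What happened | steroids given, discharged undelivered | any hospitalization |
| Transfers | not mentioned | not mentioned |

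The rule covers the problem and more. An admission before steroids could have been given cannot conceal a steroid course.

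**Step 2: avoidable loss of precision.** Let f be the share excluded by the rule and s the share of those exclusions that are irrelevant. The rule keeps 1 − f of the cohort; a rule limited to relevant admissions keeps 1 − f(1 − s). With the standard error proportional to 1/√n, exclusions spread evenly over gestational age, and the same residual variance and steroid jump under both rules, the ratio of standard errors is √[(1 − f(1 − s)) / (1 − f)].

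Worked case, f = 20% and s = 50%: the rule leaves 16,000 × 0.80 = 12,800 and the narrower rule leaves 16,000 × 0.90 = 14,400, so the ratio is √(14,400/12,800) = 1.061.

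| f | s = 25% | s = 50% | s = 75% |
|---|---|---|---|
| 10% | 1.014 | 1.027 | 1.041 |
| 20% | 1.031 | 1.061 | 1.090 |
| 30% | 1.052 | 1.102 | 1.150 |

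The range is about 1% to 15%. The ratio does not depend on the cohort size, so it applies equally to the smaller set with EDI data under the same assumptions.

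**Step 3: do early admissions cause bias?** They occur before a woman reaches the threshold and cannot respond to it. Their share should be smooth across 34+0, so they have no evident effect on the size of the jump.

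**Step 4: what transfers could do, if they are excluded.** Let a and b be the transferred shares just below and just above 34+0, D the mean outcome difference (transferred minus not transferred, equal on both sides) and F the steroid jump. If the full-cohort mean is continuous, the retained means are that mean minus aD below and minus bD above. The spurious jump (below minus above) is (b − a)D, or (b − a)D/F in the per-protocol ratio.

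- a = b: (b − a)D = 0.
- a = 10%, b = 5%, D = −2 EDI points: (0.05 − 0.10) × (−2) = 0.10 points; with F = 0.4, 0.10/0.4 = 0.25.
- a = 20%, b = 5%, D = −5: (0.05 − 0.20) × (−5) = 0.75 points; with F = 0.4, 0.75/0.4 = 1.9; with F = 0.2, 0.75/0.2 = 3.75.

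Against the 5-point threshold, the result runs from nothing to a material part, depending entirely on inputs that the documents do not give.

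**The case against.** The strongest reply is that this is a secondary estimate which the protocol already treats with caution, and that the transfer argument is conjecture. Much of this stands.

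- A reader might infer that transferred women are dropped and that the subgroup is therefore biased at 34+0. The documents do not support this. They say the discharge file covers transfers; they do not say that a transfer record counts as a prior hospitalization, and the protocol's own example is discharge without delivering. How hospital records are joined into episodes may also be settled in a later document. No transfer rate, transfer policy or step at 34+0 is given, and equal shares of comparable women give no bias.
- Excluding transferred women may serve the stated aim. The steroid variable covers only the delivery admission, so a course given at the sending hospital may go unrecorded. Putting these women back could restore that under-documentation, which the protocol itself says shrinks the steroid jump and inflates the per-protocol effect. Always including them is therefore not a safe rule either.
- A reader might also infer that the primary analysis is misdated, because a woman first seen at 33+6 and transferred could be recorded at 34+0. The protocol says "We will use gestational age in days at the time of maternal admission for the delivery as our unit of analysis" but not which admission that is for a transferred woman. That is a separate question about dating and not a consequence of this restriction.
- It would be too strong to say that the restriction loses precision for nothing. Excluding women admitted when steroids were possible is its purpose.

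The reply does not answer the missing gestational-age limit. The rule is explicit, it is wider than its stated reason, and it supplies the main per-protocol estimates.

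**Conclusion.** The concern holds in a limited form. The exclusion is broader than its purpose, and admissions before steroids were possible cost precision without reducing misclassification. On assumed inputs (10% to 30% excluded, a quarter to three quarters of them irrelevant) the avoidable increase in standard error is about 1% to 15%. These early admissions are no evident source of bias.

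The handling of transfers is an open risk. It matters only if transfers count as prior hospitalizations and if their frequency, or how transferred women differ from the rest, changes at 34+0. The documents establish neither condition, so neither the presence nor the direction of a bias can be claimed.

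The effect is confined to the per-protocol estimate. The intention-to-treat coefficient remains the primary estimate and is not altered by this restriction. This is a cheap improvement to a secondary estimate and does not threaten the main conclusion.

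**What to change.** 1. Limit the exclusion to earlier admissions at gestational ages when fetal-lung steroids could have been given, with a lower bound that the investigators state and justify. The protocol's own guideline statement starts at 26 weeks.
2. Fit the same discontinuity model at 34+0 with exclusion for prior admission as the outcome, and repeat the planned comparability checks within the subgroup. If the excluded share jumps, do not use the subgroup as the main source of the per-protocol estimate.
3. Say how transfers into the delivery hospital are treated, and report the subgroup estimate both ways: transferred women included, as one episode dated from the first admission, and transferred women excluded. Both are needed because inclusion may restore undocumented steroid use and exclusion may select differently at the cut-off.

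The cost is a few sentences in the plan and slightly more programming on hospital records that the study is already to link; no new data are needed. The downside is that some steroid use may remain undocumented, particularly where transferred women are included.

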#### Assessing comparability of groups

We will assess comparability around the 34+0 week cut-off by plotting maternal-fetal characteristics according to gestational age. Specifically, we will examine maternal age, parity, pre-pregnancy BMI, smoking in pregnancy, neighbourhood income quintile, fetal sex, diabetes status, pre-eclampsia status, mode of delivery (Cesarean vs vaginal), type of labour onset (spontaneous vs iatrogenic vs none), placental abruption, and fever in labour/chorioamnionitis. We have no reason to believe these factors will change discontinuously at 34 weeks, but will control for them in our models in the event of meaningful differences.

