### Statistical analysis

We will isolate the effects of antenatal corticosteroid administration practices using a regression discontinuity design. This design exploits the fact that an infant's probability of receiving antenatal corticosteroids changes significantly based on whether its mother presented to hospital before or after

the 34 week gestational age cut-off. The design assumes that infants immediately below the 34-week threshold are exchangeable with those immediately above the threshold except for the probability of receiving antenatal steroids, mimicking random treatment assignment. In the absence of any treatment effect, outcome rates should be smooth across the 34-week threshold, therefore any estimated change in the outcome at 34 weeks can be assumed to be due to antenatal corticosteroid treatment.

We will implement the design using a multivariable quantile regression model estimating the 50th percentile (for our primary outcome of EDI scores), multivariable log-binomial models (for binary outcomes such as developmentally vulnerable, special needs, and lower respiratory tract infection hospitalization in the first two years of life), and pooled logistic regression models (for binary outcomes where children born in different study years have follow-up time such as ADHD and asthma). In the event that our log-binomial models fail to converge, we will use logistic regression and convert odds ratios to risk ratios using postestimation commands.

Our primary model will include delivery admissions between 31+0 and 36+6 weeks. We will weight observations according to their proximity to the cut-off of 34+0 using a triangular kernel, such that observations closest to the discontinuity are assigned greater weight and those furthest from the discontinuity are given less weight. This weighting is particularly important in this cohort as the probability of birth increases with advancing gestational age, so the largest number of observations will occur furthest from the discontinuity (i.e., at 36+6 weeks).

We will use standard regression discontinuity methods to estimate the size of the discontinuity in child health outcomes due to crossing the threshold at 34+0 weeks (Lee & Lemieux 2010). We will estimate the following regression models for individuals in our sample using a 3-week bandwidth around the gestational age threshold:

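### The response to an imbalance at 34+0 is adjustment that may include factors settled after admission, and no check of daily admission counts at the cut-off is planned

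*Protocol*

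**What the plan says.** **Running variable.** Protocol, Exposure measurements: "We will use gestational age in days at the time of maternal admission for the delivery as our unit of analysis".

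**Identifying assumption.** Protocol, Statistical analysis: "The design assumes that infants immediately below the 34-week threshold are exchangeable with those immediately above the threshold except for the probability of receiving" steroids. The same paragraph attributes any change in outcome at 34 weeks to steroid treatment.

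**Cohort.** Study population takes all singleton delivery admissions from 31+0 to 36+6 and is not limited to spontaneous labour. The Introduction counts "pregnancy complication indicating an early delivery" among the reasons for giving steroids, and iatrogenic onset is a category in the comparability list.

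**Comparability check.** Protocol, Assessing comparability of groups: "We will assess comparability around the 34+0 week cut-off by plotting maternal-fetal characteristics according to gestational age". Eight of the twelve listed factors are "maternal age, parity, pre-pregnancy BMI, smoking in pregnancy, neighbourhood income quintile, fetal sex, diabetes status, pre-eclampsia status". The other four are "mode of delivery (Cesarean vs vaginal), type of labour onset (spontaneous vs iatrogenic vs none), placental abruption, and fever in labour/chorioamnionitis".

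**Response to imbalance.** Same section: "We have no reason to believe these factors will change discontinuously at 34 weeks, but will control for them in our models". The sentence goes on to make this conditional on differences being meaningful. No criterion is given, and nothing separates factors known before admission from those arising after it.

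**Other pre-specified sensitivity analyses.** These are alternative outcome definitions, exclusion of women with prior admissions, and narrower windows (32+0 to 35+6; 33+0 to 34+6). None concerns the number of admissions per day around 34+0.

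**The concern.** There are two separate problems.

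*Adjustment.* The coefficient on being below 34+0 is the primary estimate. A factor settled after admission may itself be changed by being below the cut-off. If it also shares unmeasured causes with child development, conditioning on it opens a non-causal path and moves the coefficient even when the design is sound.

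*Sorting.* The admission date of an iatrogenic delivery can plausibly be timed by clinicians who know the guideline cut-off. That is an inference from the Introduction and the comparability list; the protocol does not say it happens. If it does, the two sides differ in case mix. A jump in a characteristic fixed before admission is evidence against exchangeability, and controlling for what was measured leaves the unmeasured part in place.

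The analysis is most exposed to sorting close to the cut-off: the triangular kernel gives those days the most weight, and the narrower windows keep them and increase their influence.

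**Working it through.** The protocol states no figure on this point, so there is none to reproduce.

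**1. Classifying the twelve factors against admission**

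- Fixed or usually known before admission: 8 of 12, the first list quoted above. Pre-eclampsia belongs here only if diagnosed before admission.
- Settled, or possibly settled, after admission: 4 of 12. Mode of delivery always is. Fever in labour/chorioamnionitis often is. Labour onset (in women admitted before labour) and abruption can be.

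**2. Upper bound on a false jump from sorting**

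Assumptions, none from the protocol: equal numbers n on each side; a share s of a deferrable type on each side; children of that type differ by d EDI points; every such woman below the cut-off moves above it.

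- Below: share of the type becomes 0.
- Above: 2sn of n + sn women, a share of 2s/(1+s).
- False jump = 2sd/(1+s).

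| s | d | jump |
|---|---|---|
| 0.05 | 2 | 0.20/1.05 = 0.19 |
| 0.05 | 5 | 0.50/1.05 = 0.48 |
| 0.10 | 2 | 0.40/1.10 = 0.36 |
| 0.10 | 5 | 1.00/1.10 = 0.91 |

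If the deferred type does worse, the steroid side looks better by this amount; if it does better, the steroid side looks worse. This is a difference in means, whereas the planned primary model is a median regression.

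**3. Illustrative simulation, true effect zero**

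From the protocol: about 16,000 admissions, 31+0 to 36+6, cut-off 34+0, separate linear trends, triangular kernel. Assumed: 30% iatrogenic; unmeasured severity worth 2 points per SD; residual SD 7; severity and iatrogenic onset each raising the log-odds of Cesarean by 1; a fraction f of the less severe iatrogenic admissions due at 33+0 to 33+6 held to 34+0 to 34+2. Weighted mean regression was used, with 200 replicates. With neither sorting nor an effect on mode of delivery, the jump was -0.01.

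*Sorting only:*

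| f | unadjusted | + labour onset | + onset and mode of delivery | jump in iatrogenic share | admissions, 3 days below vs above |
|---|---|---|---|---|---|
| 0.25 | -0.13 | -0.13 | -0.11 | -0.06 | 889 vs 1,130 |
| 0.50 | -0.26 | -0.26 | -0.21 | -0.12 | 853 vs 1,210 |
| 0.75 | -0.42 | -0.43 | -0.35 | -0.18 | 824 vs 1,284 |

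With no sorting the counts were 922 vs 1,062. Adjustment removes little of the false jump. The daily counts react, and so does the iatrogenic share that the protocol will plot.

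*No sorting, but being below 34+0 changes mode of delivery:*

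| log-odds | without mode of delivery | with onset and mode of delivery |
|---|---|---|
| 0.5 | -0.03 | +0.13 |
| 1.0 | +0.04 | +0.36 |

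Here the adjustment creates the bias.

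*Both together (f = 0.50, log-odds 0.5):* -0.29 unadjusted and -0.08 adjusted. The two biases partly cancel under these inputs, which is not a repair.

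**4. Scale**

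The protocol calls 5 points on the total EDI clinically significant. If that were the effect of steroids themselves, the jump at the cut-off would be 5 times the jump in steroid use. At an assumed 0.2 to 0.6 this is 1 to 3 points.

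**The case against.** *Adjustment is conditional and mostly harmless.* A reader might infer that any imbalance triggers adjustment for post-admission variables. The text does not support that: differences must be judged meaningful, eight of the twelve factors precede or usually precede admission, and only mode of delivery follows it with certainty. What remains is that the rule covers all twelve factors and leaves the trigger undefined.

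*Sorting is not unchecked.* This stands in part. Labour onset, pre-eclampsia and abruption are plotted by gestational age, and in the simulation sorting moved the iatrogenic share by 0.06 to 0.18. But the plot is informal, has no decision rule, and does not show whether admissions bunch at 34+0. Using age at admission also means that postponing delivery after admission cannot move a woman across the cut-off; deferring the admission itself still can.

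*The direction is unknown.* A reader might infer that higher-risk pregnancies are held to 34+0 and that this hides steroid harm. The documents do not say who, if anyone, is held. The simulation held less severe cases and made the steroid side look worse.

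*A separate statistical analysis plan may cover this.* Possibly, but this document calls itself the pre-analysis plan, lists its sensitivity analyses as pre-specified, and itself contains the adjustment rule. Its reference to standard regression discontinuity methods concerns estimating the jump and names no check on sorting.

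**Conclusion.** The point holds in limited form. The rule as written allows the primary coefficient to be adjusted for mode of delivery and intrapartum fever/chorioamnionitis, which can introduce bias, and treats adjustment as the remedy for imbalance when it cannot restore exchangeability on unmeasured factors. No section examines daily admission counts at 34+0.

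The size is uncertain. The 0.2 to 0.9 points is a ceiling on assumed inputs, with either sign; the simulated false jumps were at most about 0.4 points in size, also on assumed inputs. These are small against the 5-point criterion but less so against an intention-to-treat jump of 1 to 3 points.

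Nothing in the documents shows that sorting occurred. Nor would a jump in mode of delivery, labour onset or fever prove it, since treatment may have caused the jump. This should be corrected before outcomes are analysed; it does not invalidate the design.

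**What to change.** In Assessing comparability of groups:

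1. Limit adjustment to characteristics fixed before admission: maternal age, parity, pre-pregnancy BMI, smoking, income quintile, fetal sex, diabetes, and pre-eclampsia if diagnosed before admission.
2. Do not adjust for mode of delivery, intrapartum fever/chorioamnionitis, or labour onset and abruption arising after admission. Report these descriptively, noting that a jump may reflect treatment or sorting.
3. Replace the undefined meaningful difference with estimated jumps, and confidence intervals, in the pre-admission characteristics from the same regression discontinuity model. Use these as the falsification check.
4. Add a density-continuity check of daily admission counts at 34+0, overall and by labour-onset type. It should test for a break in the trend, since counts rise with gestational age anyway. The overall count should lead, because onset type can itself be settled after admission.
5. Add a donut sensitivity analysis omitting the days next to the cut-off, for example 33+6 and 34+0, then 33+5 to 34+1.
6. State that a failed density or pre-admission covariate check limits the causal claim and is not resolved by adjustment.

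Cost: plan wording and short analyses on data already held. The donut estimate is less precise, as it drops one or two of 21 daily values per side, those with the highest kernel weight, and it removes only sorting that falls within the omitted days.
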